### Study design, setting, and participant

This is a prospective, randomized, single-center, open-label phase II trial, which takes place in the Gastrointestinal Cancer Center of Peking University Cancer Hospital and Institute, China (Fig. 1). Adult ambulatory patients aged 70 and above, with Karnofsky Performance Status (KPS) ≥ 70, histology proved gastric cancer, cT2-4aNanyM0 (UICC TNM staging 7th edition), and no prior cancer treatment, will be screened for inclusion and exclusion criteria (Table 1) by the reception oncologist. Eligible patients will be invited for study participation at their first visit at the Gastrointestinal Cancer Center. The doctor who sees the patient will give a formal and detailed description of the study and its procedures. Upon the acquisition of patient written informed consent form, patients will undergo oncology evaluation (e.g. abdominal enhanced CT and/or MRI scan, chest plain scan CT, cervical lymph node, ultrasonography, pelvic ultrasonography/CT, serum tumor markers, laparoscopic exploration and free cytological examination of peritoneal cavity) as well as geriatric assessment with G8 screening tool. Patients will afterwards be randomized 1:1 to either laparoscopic or open surgery arm by the data manager in the team using random number table. None of patients, surgeons, or data analysts will be blinded.

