### Statistical analysis

On the basis of prior research, the conventional open surgery group is expected to have a 30-day postoperative complication rate of 35%. After the repeated discussion among investigators, a consensus was reached that a 19% decrease in the complication rate was considered as superiority of laparoscopic gastrectomy over conventional open approach. PASS software returned a sample size of 164 (82 per arm) is planned, with a type I error of 0.05 (two-sided) and a statistical power of 80%. The total sample size needed is 180 (90 per am) after taking into account of a 10% dropout rate.

Data analysis will be performed on both intention-to-treat and per-protocol basis. Outcome data obtained from all participants will be included in the intention-to-treat analysis, regardless of protocol adherence; whereas in the per-protocol analysis, data of non-adherers will be excluded. For variables with a significant amount of missingness, multiple imputations will be conducted for the purpose of sensitivity analysis. Of the clinical and pathological characteristics, categorical data will be presented as number and percentage and continuous variables as mean and standard deviation if normally distributed or as median and range if otherwise. The primary analysis in this study aims to compare the between-group difference in 30-days postoperative complication rate, reoperation rate, readmission rate, and mortality rate. Pearson’s Chi-squared tests or Fisher’s Exact tests, as appropriate, will be performed for this purpose. For the continuous variables of secondary outcomes, this will be done by independent samples t-tests or Mann-Whitney U tests, as appropriate. The overall survival curves will be constructed as time-to-event plots using the Kaplan–Meier method. Log-rank tests will be used to make a simple comparison of the survival curves. Disease-free survival will be analyzed in the same manner. Proportional hazard Cox regression adjusted for variables will be employed when necessary. Subgroup analyses will be conducted by G8 score, age group, TNM stage, tumor location, laparoscopy-assisted or total laparoscopic gastrectomy, distal or total gastrectomy, and comorbidities status. All statistical analyses will be conducted in standard statistical software such as SAS and STATA with a significance level of 0.05 (two-sided).

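### The unadjusted test of the complication rate is valid, but adjusting for baseline risk factors the trial already records would probably add a few points of power

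*Protocol article*

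**What the plan says.** The protocol's Statistical analysis section defines the target: "The primary analysis in this study aims to compare the between-group difference in 30-days postoperative complication rate, reoperation rate, readmission rate, and mortality rate". It then fixes the method: "Pearson’s Chi-squared tests or Fisher’s Exact tests, as appropriate, will be performed for this purpose". No covariate-adjusted analysis is named for these rates. The only adjusted model in the section is a Cox regression, to be used if needed, which follows the survival analyses.

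The same section sizes the trial on the complication rate. It assumes 35% with open surgery and states that "a 19% decrease in the complication rate was considered as superiority of laparoscopic gastrectomy over conventional open approach". At two-sided 0.05 and 80% power, "PASS software returned a sample size of 164 (82 per arm) is planned", raised to 180 for dropout.

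Baseline risk information is collected. Under Study design, setting, and participant, patients have a "geriatric assessment with G8 screening tool" before they are randomised. Demographics are taken at baseline (Data collection). The risk variables reappear only here: "Subgroup analyses will be conducted by G8 score, age group, TNM stage, tumor location", in a list that ends with comorbidity status.

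**The concern.** The Background attributes the high complication risk of elderly patients to lower functional reserve and more comorbidity. The protocol therefore treats variables of this kind as prognostic and records several of them, but uses them only to split the sample into subgroups. With 90 per arm that is a weak use of them.

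Pre-specified adjustment of the main comparison for prognostic baseline variables usually makes it more precise at the same sample size. The trial is sized at 80% power for a fall from 35% to 16%, which more than halves the open-surgery rate. If the true effect is smaller, power drops below 80%, so precision that needs no extra patients is worth having.

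**Working it through.** **Inputs.** From Statistical analysis: 35% with open surgery, a 19-point fall (to 16%), two-sided 0.05, 80% power, 82 per arm. From Background: surgery-related mortality of 3.8–9.5%. Assumed, because the protocol gives no value: the prognostic strength of the covariates, expressed as R² (share of outcome variance explained) or as a c-statistic.

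**1. The plan's own figure.** With pooled variance and no continuity correction,

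n per arm = [1.960·√(2·p̄·q̄) + 0.842·√(p₁q₁ + p₂q₂)]² / d²

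p̄ = (0.35 + 0.16)/2 = 0.255, so 2·p̄·q̄ = 2 × 0.255 × 0.745 = 0.380. p₁q₁ + p₂q₂ = 0.2275 + 0.1344 = 0.3619. d² = 0.19² = 0.0361.

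n = (1.208 + 0.506)² / 0.0361 = 81.4, rounded up to 82. This matches the stated 82 per arm. A 19% relative fall would need 768 per arm, so the absolute reading is the one used. Power of the unadjusted test is 80.3% at 82 per arm and 83.8% if all 90 per arm are analysed.

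**2. Gain by formula.** Adjustment acts roughly as an effective sample size n/(1 − R²). For example, R² = 0.10 gives 82/0.90 = 91.1 per arm and power 84.3%.

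**3. Gain by simulation.** At 82 per arm with four baseline covariates, the unadjusted test was compared with (a) the Wald test from the adjusted logistic model, 4,000 runs per setting, and (b) the standardised risk difference from such a model, in two separate sets of 4,000 and 3,000 runs. With 4,000 runs the Monte Carlo error is about 0.6 points. Simulated cells show unadjusted v adjusted power in per cent.

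| Assumed strength | Formula | (a) Logistic Wald | (b) Risk difference, 4,000 runs | (b) Risk difference, 3,000 runs |
|---|---|---|---|---|
| None (R² = 0) | 80.3 | 80.8 v 80.4 | no loss seen | 81.2 v 81.5 |
| Weak (R² about 0.05, c about 0.64) | 82.3 | 80.4 v 81.6 | 80.4 v 82.5 | 80.5 v 81.9 |
| Moderate (R² about 0.09–0.10, c about 0.69) | 84.3 | 79.5 v 82.1 | 79.5 v 83.4 | 80.9 v 84.5 |
| Strong (R² about 0.15, c about 0.74) | 86.3 | 81.4 v 86.2 | 81.5 v 87.3 | 81.6 v 87.3 |

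For the risk difference the gains in the 4,000-run set are 2.1, 3.9 and 5.8 points. In the 3,000-run set they are 1.4, 3.6 and 5.7 points.

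**4. Type I error.** With the plain delta-method variance the standardised risk difference gave about 6% in the 4,000-run set. The 3,000-run set gave 4.9–5.3%. The test may therefore be slightly liberal at this sample size, and the variance method needs care.

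**5. How many covariates the data carry.** Expected complications are 82 × 0.35 + 82 × 0.16 = 28.7 + 13.1, about 42. Treatment plus four single-parameter covariates makes five parameters, or about 42/5 = 8 events each.

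**6. The other primary components.** At the cited mortality, deaths per 90 patients would be 90 × 0.038 = 3.4 to 90 × 0.095 = 8.6. A model with several covariates is hardly workable there.

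**The case against.** The strongest reply is that nothing here is wrong. An unadjusted 2×2 test is valid under 1:1 randomisation, it is the test the trial was sized for, and it delivers the stated power. All of that stands. A reader might infer that the chi-squared test is a mistake or that it leaves the trial short of its planned power. Step 1 of the working shows neither.

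A reader might also infer that chance imbalance in age or G8 goes uncorrected and biases the result, particularly as no stratification is described. The document does not support this. The type I error of the unadjusted test already allows for chance imbalance. The article is a condensed account, so its silence on stratification or on a supporting adjusted analysis shows nothing about the full protocol or analysis plan.

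Third, the size of the gain is assumed. The Background explains why elderly patients are at higher risk. It does not say how well these variables discriminate among patients already selected for age 70 and above, Karnofsky 70 or more, no serious heart disease and adequate organ function (Table 1). Selection of this kind is likely to weaken them. This stands, and is why the gain is given as a range starting at zero.

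Fourth, adjustment is not free. Comorbidity status is undefined in the article, coding and missing-value rules are needed, and about 42 events limit the model. A logistic coefficient would also move the target to a conditional odds ratio. The last point is met by reporting a standardised risk difference, which is on the same scale as the 35% v 16% used for sizing. The others stand as small costs.

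**Conclusion.** The point holds as a recommended efficiency improvement. The protocol states its primary test plainly, and a better-powered analysis is available from data the trial already collects. The gain for the complication rate is about 0 points of power if the covariates are not prognostic, about 2 to 4 if they are weak to moderate, and about 6 if they are strong (c-statistic near 0.74). These figures rest on 35% v 16%, 82 per arm, and an assumed prognostic strength for which the protocol offers no evidence. No loss of power appeared with non-prognostic covariates beyond simulation error. The stronger claim, that the gain is certain and costs nothing, is not supported. The recommendation does not extend to reoperation, readmission or mortality.

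**What to change.** Add one paragraph to the analysis plan before anyone sees outcome data by arm, including at the interim analysis planned when half the patients are randomised. In an open-label trial, adjustment chosen after that would carry little weight. The paragraph should state:

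- **Primary analysis of the complication rate:** logistic regression on arm, continuous age, G8 score, comorbidity status as one term and tumour location as one term, all as known before randomisation. Report the standardised risk difference with 95% CI.
- **Variance:** a robust or small-sample estimator, or a bootstrap, because the plain delta-method variance may be slightly liberal here.
- **Limits:** about five parameters in all. Surgical subgroup factors settled only at operation, such as laparoscopy-assisted v totally laparoscopic, do not belong in the model.
- **Rules fixed in advance:** the definition of comorbidity status, the coding of location, and the handling of missing covariate values.
- **Sensitivity analysis:** the Pearson test as now planned.
- **Reoperation, readmission and mortality:** Pearson or Fisher tests, unchanged.

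The cost is the drafting and the prior agreement on these rules. No extra patients or data are needed, and the sample size can stay as it is.

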### Interventions

All patients will receive surgery within one week after randomization. Perioperative enteral/parenteral nutrition support will be allowed for patients with nutritional risk. The patients will be fasted of food and water 1 day and 4 h before the surgery, respectively. Patients will not normally receive preoperative gastrointestinal decompression, except for those with digestive tract obstruction. Prophylactic use of antibiotics during the perioperative period will be in accordance with relevant national regulations. All patients with pathology proved advanced gastric cancer will be suggested to use adjuvant chemotherapy, the regimen of which will be in line with the Japanese Gastric Cancer Treatment Guideline (version 5th) [11].

A standard laparoscopic or open radical gastrectomy will be performed by two experienced surgeons for all enrolled patients. In the open group, an approximately 20- to 25-cm incision will be made from the falciform process to the periumbilical area [12]. In the laparoscopic group, one 10-mm trocar for the camera will be inserted below the umbilicus [12]. Another three 10-mm ports will be inserted in the left upper quadrants 2 cm below left lower rib margins, the right and left flank areas, respectively [12]. One 5-mm trocar will be lastly placed at the right upper quadrants 2 cm below right lower rib margins [12]. Pneumoperitoneum will be achieved using carbon dioxide with a pressure maintained at 8-12 mmHg. Greater omentum resection, lymph node dissection, and vascular treatment will be performed under laparoscopy. Gastrectomy and digestive tract reconstruction may be performed by the surgeon under laparoscopy or assisted incision, as appropriate. All abdominal operation of laparoscopy will be videotaped. Anastomosis will be performed using the instrumental method. The specimen will be pulled out through a small median incision under the xiphoid (about 3–8 cm). In both groups, the range of gastric resection and lymph nodes dissections will be done in accordance with the Japanese Gastric Cancer Treatment Guideline (version 5th) [11]. Surgeons will decide the digestive tract reconstruction approach according to the intraoperative circumstances. Considering the healing capacity of elderly patients, local drainage will be placed on both sides of the anastomotic stoma.

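### The planned subgroup by assisted versus totally laparoscopic technique exists in one arm only and is set after randomisation, so it cannot yield a laparoscopic-versus-open effect

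*Protocol article*

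**What the plan says.** The Statistical analysis section lists seven subgroup factors in one sentence: G8 score, age group, TNM stage, tumour location, then "laparoscopy-assisted or total laparoscopic gastrectomy, distal or total gastrectomy", and finally comorbidity. It treats all seven alike, does not say what is to be compared within them, and marks none as descriptive. The same section sets a two-sided 0.05 level for all analyses.

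Three other statements bear on the technique factor:

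- **What is randomised.** Under Study design, setting, and participant, patients are "randomized 1:1 to either laparoscopic or open surgery arm". Nothing finer is allocated. The same section states: "None of patients, surgeons, or data analysts will be blinded".
- **When surgery happens.** Under Interventions: "All patients will receive surgery within one week after randomization".
- **Who chooses the technique.** In the description of the laparoscopic procedure under Interventions: "Gastrectomy and digestive tract reconstruction may be performed by the surgeon under laparoscopy or assisted incision, as appropriate". The open procedure is different in kind: "In the open group, an approximately 20- to 25-cm incision will be made from the falciform process to the periumbilical area".

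**The concern.** A subgroup analysis in a two-arm trial asks whether the effect of treatment differs between kinds of patient. It needs a factor that patients in both arms possess and that allocation cannot influence. G8 score and age meet both conditions. Assisted versus totally laparoscopic meets neither: it describes how one of the two treatments was delivered.

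An analyst who follows the list must still produce something for this factor. One option is to set each technique group against the whole open arm. The other is to compare the two techniques with each other. In both, the groups are formed by an unblinded surgeon's judgement, so a difference may reflect which patients were given which technique. Placed beside true baseline subgroups and tested at 0.05, such a result could be read as randomised evidence on technique. The Discussion intends the data to support later phase III trials, so a misreading could carry forward.

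**Working it through.** **1. The plan's own figure.** Inputs from the Statistical analysis section: 35% complications in the open arm, a 19% decrease (read as percentage points, so 16%), two-sided alpha 0.05, power 80%. With pooled variance under the null and mean rate 0.255:

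n per arm = [1.96·√(2·0.255·0.745) + 0.8416·√(0.35·0.65 + 0.16·0.84)]² / 0.19² = (1.208 + 0.506)² / 0.0361 ≈ 81.4, so 82.

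This gives 164 in total, as stated. (A relative 19% reduction would need 768 per arm, so the absolute reading is the intended one.) Allowing for 10% dropout, 164/0.9 = 182.2, close to the stated 180. None of this depends on the subgroup list, and nothing below changes it.

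**2. The structure of the factor.** Planned numbers by allocated arm:

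| Level | Laparoscopic arm | Open arm |
|---|---|---|
| Laparoscopy-assisted | some of 90 | 0 of 90 |
| Totally laparoscopic | some of 90 | 0 of 90 |

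Within each level the open-arm rate has a denominator of zero, so the between-arm difference is undefined. An interaction is the difference between two such differences, so it is undefined too. More patients would not help.

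**3. What can be computed.** (a) One technique group against all 90 open patients; (b) assisted against totally laparoscopic within the laparoscopic arm. Neither is protected by randomisation. If the laparoscopic arm happened to split evenly (an assumption), (b) would compare 45 with 45 and have about 54% power for a 19-point difference.

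**4. How large selection bias could be.** This is an illustration only. The documents give no split and no selection rule. Assumptions: 90 per arm; true rate 35% in both arms; no effect of arm or technique; each arm half lower-risk and half higher-risk; all 45 lower-risk laparoscopic patients receive the totally laparoscopic technique. The test is Pearson's chi-squared, rejecting when |p₁ − p₂| / √[p(1 − p)(1/n₁ + 1/n₂)] > 1.96, with 200,000 simulated trials per row.

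| Lower/higher risk | Apparent benefit, totally laparoscopic v all open | False positives, (a) | False positives, (b) | False positives, full randomised comparison |
|---|---|---|---|---|
| 35% / 35% (no selection) | 0 points | 5% | 5% | 5% |
| 30% / 40% | 5 points | 9% | 17% | 5% |
| 25% / 45% | 10 points | 21% | 53% | 5% |
| 20% / 50% | 15 points | 44% | 87% | 4% |

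If the higher-risk half received the totally laparoscopic technique instead, the apparent differences would change sign: 35 − 40 = −5, 35 − 45 = −10 and 35 − 50 = −15 points. The table shows that selection can matter at these sample sizes. It does not show which way selection runs in this trial.

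**The case against.** The strongest defence is that the sentence names no comparison. Because the factor exists only among laparoscopic patients, a within-arm comparison is a natural reading, and it would be legitimate if labelled as non-randomised. A statistical analysis plan that is not shown might say so. It is also one of seven secondary factors, and no stated objective or hypothesis rests on it. This limits the weight of the point but does not remove it: the protocol itself places the factor among ordinary subgroups, without a label, and in that role it cannot work.

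Several stronger readings are tempting, and the document does not support them.

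- **That harder cases go to the assisted incision, so the analysis will favour totally laparoscopic surgery.** The Interventions section leaves the choice to the surgeon without giving a criterion. Habit, tumour site or type of resection could drive it.
- **That the conversion rules fix the direction.** Patients converted for large confluent nodes or severe intraoperative complications would fit neither level if classified by the technique completed. But the article does not say how they would be classified, so this too shows only a possibility.
- **That the plan compares selected laparoscopic patients with all open patients.** It permits this but does not state it.
- **That the sentence "Surgeons will decide the digestive tract reconstruction approach according to the intraoperative circumstances" shows the factor is decided during the operation.** It follows a statement about both groups and concerns the type of reconstruction. That technique is settled after randomisation rests on the order of events and the surgeon's discretion.
- **That TNM stage and distal versus total gastrectomy are equally defective.** Both exist in each arm and can be compared between arms. A problem would arise only if values came from the operation or the pathology report, which the article does not say.

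**Conclusion.** The point holds in a limited form. As a treatment-effect subgroup, assisted versus totally laparoscopic is unusable: with no open patient in either level, neither a within-level effect nor an interaction exists. This follows from the randomisation scheme and the description of the procedures and needs no numerical assumption. Any comparison that can be made is non-randomised and open to selection bias of unknown direction and size. The rates of 9% to 44% for part of the laparoscopic arm against all open patients, and 17% to 87% within the arm, rest wholly on the assumed even split and assumed risk-based choice.

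The primary comparison of 30-day outcomes, the 164 evaluable patients and the 180 to be recruited are unaffected. The point is a modest one about a secondary analysis, but worth correcting before the data are seen.

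**What to change.** Remove assisted versus totally laparoscopic technique from the list of treatment-effect subgroups. Report it only as a description of the laparoscopic arm, stating that the groups were not randomised, and make no test of part of that arm against the open arm.

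For the remaining factors, state that they are defined by values known before randomisation where these are recorded: clinical TNM stage, G8 score, age and comorbidity. Clinical stage is already an eligibility item in Table 1, and G8 is assessed before allocation. Distal versus total gastrectomy should likewise be taken as planned. Table 1 requires only that one or the other be feasible and does not show that the individual plan is recorded, so this may need one added baseline field.

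The cost is a few words in the protocol or statistical analysis plan and, at most, that one field. Sample size, treatment and trial conduct do not change.

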### Data monitoring, auditing, and interim analysis

Data monitoring and auditing will be conducted by the funding agency annually. An interim-analysis will be performed by an independent statistician when half of the patients have been randomized. The trial will be stopped if one treatment is found to be statistically more beneficial or harmful than the other.

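### Taken as written, the half-way stopping rule and the blanket 0.05 level test the same hypothesis twice at 0.05, giving a type I error of about 8.3% for one endpoint instead of the stated 5%

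*Protocol article*

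**What the plan says.** The section on data monitoring, auditing and interim analysis places one look, by an independent statistician, "when half of the patients have been randomized". Its stopping rule is: "The trial will be stopped if one treatment is found to be statistically more beneficial or harmful than the other". It gives no p-value, boundary or endpoint for that look.

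The Statistical analysis section sizes the trial "with a type I error of 0.05 (two-sided) and a statistical power of 80" per cent. It closes with the only significance level in the document: "All statistical analyses will be conducted in standard statistical software such as SAS and STATA with a significance level of 0.05 (two-sided"). No exception is made for the interim or for the final test.

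The planning assumptions, from the same section, are:
- "the conventional open surgery group is expected to have a 30-day postoperative complication rate of 35" per cent
- "a 19% decrease in the complication rate was considered as superiority of laparoscopic gastrectomy"
- "PASS software returned a sample size of 164 (82 per arm) is planned"

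**The concern.** The stopping rule asks only for a statistical difference in either direction, and the only level supplied is 0.05 for everything. Together they give the null hypothesis two chances to be rejected at 0.05, while the sample-size paragraph claims 5% in total. These are statements in one document that cannot all be true.

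The superiority claim on perioperative safety is at stake. A positive result would carry more false-positive risk than declared, and a stop at half size is likely if the planned effect is real. Results that cross early also tend to overstate the effect. The problem has to be settled before the interim, because a boundary chosen after the data are seen is not credible.

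A smaller point is the trigger. Surgery may follow randomisation by up to a week (Interventions) and the primary outcomes run to 30 days after surgery (Primary endpoints). When half are randomised, the latest patients have no primary outcome yet.

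**Working it through.** **Inputs from the protocol article.** Two-sided alpha 0.05; power 80%; 35% complications with open surgery; a decrease of 19%; 82 per arm evaluable (164); 90 per arm randomised (180); 1:1 allocation; one interim at half randomisation.

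**1. Reproduce the planned size.** Read the 19% as percentage points, so 35% versus 16%, with mean rate 0.255.

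n per arm = [1.960·√(2·0.255·0.745) + 0.842·√(0.35·0.65 + 0.16·0.84)]² / 0.19² = (1.208 + 0.506)² / 0.0361 = 81.4, rounded up to **82**.

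This matches the stated figure. A relative 19% reduction would need 768 per arm, so the absolute reading is the intended one. The 82 is the single-look size.

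**2. Type I error with 0.05 at both looks.** Under the null, the interim and final statistics Z1 and Z2 are bivariate normal with correlation √t, where t is the information fraction.

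Type I error = 1 − P(|Z1|<1.960 and |Z2|<1.960)

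| t at interim | Overall type I error |
|---|---|
| 0.50 | 1 − 0.9169 = 8.31% |
| 0.45 | 8.48% |
| 0.40 | 8.63% |

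The document gives no accrual rate, so 0.45 and 0.40 are assumed values for the outcome lag. Exact binomial enumeration of the chi-squared test, for common rates of 16 to 35%, gives 8.3 to 8.5% with 41 then 82 per arm, and about 8.6% with 45 then 90 per arm.

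**3. Chance of crossing at the interim if the planned effect is true.** The final statistic has mean 1.960 + 0.842 = 2.802. At t = 0.5 the interim mean is 2.802·√0.5 = 1.981.

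P(Z1>1.960) = P(standard normal > 1.960 − 1.981) = **0.508**.

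With 41 per arm and a pooled rate of 0.255, crossing needs an observed difference of about 1.960·√(2·0.255·0.745/41) = 0.189. A trial stopped for benefit would therefore show at least about 19 points.

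**4. If only the interim is strict.** With the final test left at 0.05 and t = 0.5, the overall error is 5.02% for interim p<0.001, 5.10% for p<0.0031 and 5.22% for p<0.0056.

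**5. Boundaries that hold 5% overall (t = 0.5).** Lan-DeMets O'Brien-Fleming-type spending can be set up in two ways. Power is at the design effect, where a single look has 80.0%.

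| Spending | Interim z (p) | Final z (p) | Power |
|---|---|---|---|
| 0.025 per side | 2.963 (0.0031) | 1.969 (0.0490) | 79.9% |
| Total two-sided 0.05 | 2.772 (0.0056) | 1.979 (0.0478) | 79.7% |

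**The case against.** The strongest reply is that the article never says the interim is unadjusted. The 0.05 sentence is about software, stands in another section, and could be meant as the overall level. A journal article commonly leaves the boundary to the full protocol or SAP, and giving the look to an independent statistician suggests that one may exist. This stands in part: 8.3% holds for the rule as published and is not a proven property of the trial as run. It does not remove the point. The article does more than leave the boundary out: it states a stopping rule and a level covering every analysis. A proper boundary elsewhere would contradict that sentence.

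A reader might also infer three stronger things that the document does not support.

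- **That the single-look sample size proves the interim is unadjusted.** It does not. An O'Brien-Fleming-type plan needs only about 165 to 166 evaluable patients against 164, so 82 per arm is compatible with an adjusted interim.
- **That the error across all four primary rates has one known, larger value.** The interim endpoint is unnamed and four rates are compared, so the figure could be higher. But it depends on event rates that the document does not give for planning. With assumed rates for complications, reoperation, readmission and mortality of 25/3/5/2% it is about 12%; with 35/5/8/4%, about 16%; with 35/10/10/9.5%, about 23 to 24%. It also mixes in a separate multiplicity question.
- **That this rule uniquely costs the quality-of-life and survival comparisons half their patients.** Any early stop does that, including one under a proper boundary, and nothing says that follow-up of enrolled patients would end.

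**Conclusion.** The point holds for the text as written. It rests on three assumptions: the blanket 0.05 is the interim threshold, a stop in either direction counts as rejection, and one endpoint is tested. The lag in outcomes matters little to the error rate. If a strict interim boundary exists elsewhere, the inflation nearly disappears and what remains is a wording error in the Statistical analysis section. Either way the published rules do not deliver the declared 5% and must be corrected before the interim is run. The arithmetic is firm; how the sponsor means to run the interim is less certain.

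**What to change.** 1. In the interim analysis section, name the 30-day complication rate as the endpoint of the efficacy interim.
2. Trigger it when half the patients have completed 30 days after surgery, in place of half randomised.
3. State a two-sided boundary that holds 5% overall, and say how alpha is spent, because the label O'Brien-Fleming-type alone does not fix the thresholds. Either pair in step 5 of the working will do: 0.0031 then 0.0490, or 0.0056 then 0.0478. Recompute the final level if the information fraction differs from 0.5.
4. Amend the 0.05 sentence in the Statistical analysis section so that it excepts the interim and final tests of this endpoint and refers to the boundary.
5. If a boundary already exists in an unseen document, cite it and make steps 1 to 4 agree with it.

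The cost is about a paragraph of wording, an interim somewhat later in calendar time, and 0.1 to 0.3 percentage points of power at 164 evaluable patients. The planned 180 can stay.
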